## Abstract

**Background:**

Frail community-dwelling older adults, whom might experience problems regarding physical, cognitive, psychological, social and environmental factors, are at risk for adverse outcomes such as disability, institutionalization and mortality. People in need of help do not always find their way to care and support services and are left undetected. The aim of the D-SCOPE project is to detect frail community-dwelling older adults who previously went unnoticed and to improve their access to care and support. Goal is to increase their frailty-balance, quality of life, meaning in life, life satisfaction, mastery, community inclusion and ageing well in place.

**Methods/design:**

The study is a prospective, longitudinal randomized four-armed controlled trial with follow-up at 6 months. The study group aims to include 900 community-dwelling older adults aged 60 years and over from 3 municipalities in Flanders (Belgium). While selecting the study group, risk profiles for frailty will be taken into account. Participants will be randomly selected from the census records in each municipality. Data will be collected prospectively at baseline (T0) and at follow-up, 6 months after baseline (T1). At baseline, participants who are at least mild frail on one of the 5 domains of frailty (CFAI-plus) or feel frail based on the subjective assessment of frailty will be randomly assigned to (1) the study group or (2) the control group. A mixed method design with the inclusion of quantitative and qualitative data analyses will be used to evaluate the efficacy and experiences of the detection and prevention program on frailty.

**Discussion:**

The study will contribute to an innovative vision concerning the organization of care and support, and a timely and accurate detection and support of community-dwelling older adults at risk for frailty.

**Trial registration:**

This trial was registered at ClinicalTrials.gov, on May 26, 2017, identifier: NCT03168204.

## Background

Frailty is a common phenomenon in community-dwelling older adults. Research indicates that the average prevalence for multidimensional frailty is 13.6% and 33.5% for prefrailty in community-dwelling older adults [1]. Frailty increases with age [1, 2]. For example, a systematic review on the prevalence of frailty indicates that the prevalence for oldest-old people is 15.7% (80–84 years) and 26.1% (≥ 85 years) [1]. Within an aging society, more and more persons are confronted with frailty and the demand for care and support increases [3–6]. Although frailty has mainly been approached as a physical issue [7, 8], different researchers point to the necessity to operationalize frailty as a multidimensional and dynamic concept that considers the complex interplay of physical, cognitive, psychological, social and environmental factors [9–12]. Not only researchers identify frailty in a multidimensional way, older adults themselves experience frailty as more than merely a physical issue as well [13].

As older adults become frail, different dimensions of their lives such as their quality of life and feelings of control (e.g. mastery) may be affected [14–16], and their risk for adverse outcomes such as hospitalization and institutionalization increases [17–19]. A study by Rockwood et al. [19] indicates that frailty is one of the most important predictors of death and institutionalization. Governments are implementing a proactive care approach in order to prevent or delay (the high costs of) such institutionalization and other adverse outcomes, and stimulate older adults to stay in their own environment as long as possible with good quality of life [20]. This so-called policy on aging in place is in line with the wish of the majority of older adults [21], even when they need care and support, have economic difficulties or live in inadequate housing or deprived environments [22].

People in need of care and support do not always find the appropriate services and are often left undetected [23]. Nowadays in several European countries, also in Belgium, there is insufficient continuity and coherence between the different care and support services in the community [24]. Research indicates that 6.4% of Flemish older adults in need of care and support do not receive any care at all [25]. As a result, the problems and needs of older adults are frequently not recognized or treated in time, leading to a decline of their autonomy and quality of life. Furthermore, current initiatives to proactively identify health and social problems in (frail) older adults insufficiently address needs of (frail) older people [26]. This suggests a need for rethinking the organization of the support and care system [27]. For instance, empowering older adults to manage their own health and social issues and improving their access to community care and support needs to be ameliorated [28]. Therefore, early detection of frailty and tailored care and support are of main importance [29].

Within the detection and support of frail older adults, a critical consideration should be made. Frailty in older adults does not necessarily have negative consequences in daily life, especially when the right care and support is present. This suggest that besides measuring the deficits of frailty, there is also a need to take into account the strengths and resources of older adults [30]. Therefore, we prefer to use balancing factors and the frailty balance as terminology. The latter is in line with Baltes and Smith [31] who suggest the recognition of two faces of human aging, including both the gains and the losses. Such gains might also be seen in the context of losses, as older adults may unfold unexpected substitute skills, collaborative relationships or creative strategies to overcome limitations [32]. For instance, two individuals with a similar frailty level or profile can have different needs of support because their ‘frailty-balance’ is different [33]. Thereby, they might differ in terms of autonomy, resilience, social contacts and received informal and formal care. Interventions are necessary to close of diminish the distance of the gap between gains and losses, and to restore the frailty-balance [33]. Furthermore, older adults need to be supported in using and further develop their own competences [30].

Findings from aforementioned studies, additional literature reviews [34–36] and preliminary studies [29, 37–42] led to the design of a multidimensional detection and prevention program for frail community-dwelling older adults (D-SCOPE) aimed to improve access to care and support. Research indicates that for both men and women, increased age, having no partner, having moved in the previous 10 years, having a lower educational level and having a lower household income are risk characteristics for frailty [29]. Furthermore, different risk profiles for frailty in older adults exist according to gender and the type of frailty (physical, psychological, social, environmental and total frailty). In addition to frailty, it is also important to identify and strengthen the competences and resources of older adults [30, 40]. For example, a literature review concerning the social environment of older adults indicates that different aspects of the social environment such as subjective neighborhood characteristics are protective for frailty in community-dwelling older adults [34]. Another systematic review found a high level of physical activity and being married to be protective against developing limitations in ADLs in community-dwelling persons aged 75 years and over [35].

This article describes the design of the Randomized Controlled Trial (RCT) aimed to evaluate a detection and prevention program on frailty (D-SCOPE), which will create a continuum of care and support for frail community-dwelling older adults, from early detection, over intervention, to follow-up. The D-SCOPE frailty program intends to develop methods to easily, accurately and timely detect and prevent a negative frailty-balance in older adults. The intervention will include tailored care and support and long term care follow-up. The RCT will explore if the D-SCOPE frailty program improves the quality and efficacy of care and support given to frail community-dwelling older adults, which ultimately would increase their quality of life, meaning in life, life satisfaction, mastery, community inclusion and ageing well in place.

The objectives of this trial are to conduct:An effect evaluation to determine if the D-SCOPE frailty programdetects frail community-dwelling older adults who otherwise would have remained undetected (i.e., older adults who are at least mild frail on one of the 5 domains of frailty of the CFAI-plus or feel frail based on the subjective assessment of frailty, who do not receive the necessary care and support, by using risk profiles based on age, gender, marital status, migration background and being moved in the past 10 years [29])guides frail community-dwelling older adults towards appropriate care and support (by recognizing, valorizing and strengthening their competences, strengths and resources)prevents that care and support is discontinued (by the older person itself, the care and support organization, discontinuity or care selection by the organization) and thus reduce dropoutimproves the frailty-balance of community-dwelling older adults (i.e., effect on frailty, balancing factors and outcomes)A process evaluation to determine the obstructing and facilitating components when implementing the D-SCOPE frailty program:On the micro-level: concerning the individual capacities of key-actors (volunteers, municipal health and social care professionals, etc.) such as motivation, needed outcomes, required training and features of older adults (financial vulnerability, care expenditures, etc.)On the meso-exo-level: concerning interpersonal relations, management, administrative support, professional networks, etc.On the macro-level: concerning the broader care system, present care and support organizations in the network, political recommendations, available resources, etc.

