## Methods/design

### Study design

The D-SCOPE frailty program concerns a Randomized Controlled Trial (RCT). The RCT will compare usual care with an intervention that include tailored care and support and long-term care follow-up. Figure 1 presents an overview of the study design. The D-SCOPE frailty program will start with targeted case-finding, which refers to the selections from the census records based on eligibility criteria [29]. Older adults will receive an invitation letter explaining the purpose of the study, the way on which the study will be conducted and the expectations towards people who agree to participate. A trained volunteer or a researcher will contact them in person and will inform them face to face about the study. Participants will also receive the informed consent form and a letter for the general practitioner explaining the D-SCOPE frailty program. Respondents will have the opportunity to ask questions if anything would remain unclear. Older adults willing to participate will undergo the baseline assessment (T0) after signing the informed consent.

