**Fig. 1 Fig1:**
[figure not shown]
Flow diagram of the D-SCOPE frailty program

Older adults who are at least mild frail on one of the 5 domains of frailty (CFAI-plus) or feel frail based on the subjective assessment of frailty will be randomly assigned to either (1) the experimental group or (2) the control group. Older adults with no-to-low frailty (CFAI-plus) or who do not feel frail (subjective assessment of frailty) will be grouped into a third group. A fourth group will include frail older adults willing to participate in the T0 and T1 assessment but not in the intervention part. All groups except for the experimental group will receive care as usual.

All older participants will be assessed after a 6 months’ period. The study will include an effect evaluation and a process evaluation of the RCT. The effect study will be conducted using a quantitative evaluation of the outcome measures for frail community-dwelling older adults. The process evaluation will be performed by a quantitative monitoring of the experimental group (including follow-up telephone interviews) and qualitative focus groups with older adults, informal caregivers and municipal health and social care professionals in each municipality.

The baseline assessment T0 will begin in June 2017 until October 2017. The study assessment T1 will begin in December 2017 until April 2018. The intervention will take place between June 2017 and March 2018, between the baseline assessment T0 and the study assessment T1. The qualitative evaluation will take place in March and April 2018. The data analysis will take place between April 2018 and June 2018.

The content of the program has been developed in close collaboration with representatives of different home care and support levels, i.e. general practitioners, home care organizations, social service of the municipalities, home nurses, older people’s organizations, centers of expertise in housing and care, care insurances companies, universities, etc.

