### Intervention

The intervention contains several steps in order to empower older adults and improving their access to care and support [28]. Older participants assigned to the experimental group after the first home visit containing the T0 baseline assessment will be contacted by a professional from the social service of the municipality for a second home visit. These professionals will already be experienced with conducting home visits and will receive training and instructions concerning multidimensional frailty, frailty-balance and taking into account the strengths and competences of older adults and their informal caregivers. During the second home visit, the professional from the social service of the municipality will further explore the older adult’s competences, needs and preferences. Based on the results of the baseline assessment and on the results of the second home visit, the professional from the social service of the municipality will propose a type of intervention. The decision and organization of tailored care and support will be made together with the older participant and his/her environment. The older participant will be accompanied in the referral once decided in which organization/form of intervention the older participant will participate in order to reduce dropout. The older participant will receive tailored care and support whereby his competences, strengths and resources will be supported [30]. The intervention will depend on the availability of the care and support services in the municipality, and could be formal (e.g., home care) or informal (e.g., activities of an older adult’s association). A professional from the social service of the municipality will monitor which care the participant receives, when the older person cancels the care and support and if everything is going according to his/her wishes. This will be done monthly by telephone.

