### Measurements

Table 2 presents the outcomes of the effect and process evaluation.

**Table 2 Tab2:** SPIRIT diagram outlining schedule of enrolment, intervention and assessments for study participants

Time points		Enrolment	Baseline assessment T0	Intervention	Quantitative monitoring	Monthly follow-up	Study assessment T1	Qualitative evaluation
Introduction/preparation	Screening eligibility criteria	x						
	Information letter	x						
	Informed consent	x						
Study groups	Experimental group		x	x	x	x	x	x
	Control group		x				x	x
	Care avoiders		x				x	x
	Group ≤ mild frail (CFAI-plus) or do not feel frail (subjective assessment of frailty)		x				x	x
	Informal caregivers							x
	Municipal health and social care professionals							x
Primary outcome measures	Quality of life		x				x	
	Meaning in life		x				x	
	Life satisfaction		x				x	
	Mastery		x				x	
	Community inclusion		x				x	
	Ageing well in place		x				x	
Secondary outcome measures	Multidimensional frailty		x				x	
	Physical phenotype of frailty		x				x	
	Feeling frail		x				x	
	Resilience		x				x	
	Coping		x				x	
	Help needed for activities in daily life		x				x	
	Informal and formal care		x				x	
	Medical care		x				x	
	Leisure time		x				x	
	Neighborhood		x				x	
	Future perspective		x				x	
	Life events		x				x	
Additional variables	Socio-demographic variables		x				x	
	Socio-economic situation		x				x	
Process measures	Amount of intended target group that participated in the second home visit/started the intervention				x			
	Amount and types of delivered intervention(s)				x			
	Number refuses, dropouts and completions				x			
	Logbook				x			
	Reasons for refusal/dropout					x		
	Satisfaction of intervention					x		
	Satisfaction D-SCOPE frailty program							x
	Experiences care/support processes							x
	Components that support or inhibit the implementing process of the D-SCOPE frailty program							x

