The Comprehensive Frailty Assessment Instrument (CFAI-plus) will measure *multidimensional frailty* [12, 50]. The physical domain evaluates the general physical health (e.g., walking up a hill or stairs); the psychological domain assesses mood-disorders and emotional loneliness (e.g., feeling pressure); the social domain contains social loneliness and social support (e.g., there are enough people I feel close to); and the environmental domain evaluates conditions of inadequate housing using (e.g., my house is in a bad condition). Cognitive frailty was recently added to the CFAI and evaluates cognitive functioning (e.g., memory problems) [50]. The Fried’s phenotype of frailty (slow mobility, weakness, weight loss, decreased activities and exhaustion) [7] will be used to assess the physical phenotype of frailty as well as the questionnaire of Op het Veld et al. [51]. For weakness and slow mobility, 180 older participants will do the physical tests included in the Fried’s phenotype of frailty. The *subjective feeling of frailty* will be assessed with a self-constructed question which explores to what extent the participant agrees with the statement ‘I feel frail’. Older participants will also be asked to rate their subjective feeling of being frail on a scale from 0 to 10. *Resilience* will be measured by using the Connor-Davidson Resilience Scale (CD-RISC2), which is an abbreviated 2-item version of the original Scale [52]. *Coping* will be measured by using 6 items (i.e., active coping, positive reframing, acceptance, religion, emotional support and self-distraction) of the BRIEF Cope Carver scale [53]. By proposing statements, older participants need to answer to what extent they would react like this in a stressful or difficult situation. *Help needed for activities in daily life* will be measured by asking if older participants need help with 8 activities of daily life (i.e., personal care, household tasks, personal displacements, administrative and financial management, social company and support, grocery shopping, chores and supervision), and to what extent the help they receive for these activities is sufficient. These questions are adapted from the questionnaire of the Belgian Ageing Studies (BAS) [54]. *Informal and formal care* will be assessed by asking older participants if they receive care from 7 informal (e.g., children, neighbors, friends) and 13 formal caregivers (e.g., home nursing), and if they are satisfied with the help they receive from these caregivers. These questions are adapted versions of the BAS-questionnaire [54]. *Medical care* will be measured by asking how many times the participants needed to go to a general practitioner, a hospital, residential setting and/or rehabilitation center over the past 6 months (day care/overnight stay). These questions are adapted from the Health Interview Survey [55]. In addition, the participants will be asked when they visited a general practitioner for the last time. Also different aspects of the environment will be assessed. First, the *social environment* will be administered by using 3 items from the social cohesion dimension of the Neighborhood Scale [56]. Second, the *physical environment* will be explored by using 4 items from the BAS-questionnaire [54] as well as from the Neighborhood Environment Walkability Scale [57]. In terms of *participation*, leisure time will be measured by using an adapted question with 8 items derived from the BAS questionnaire [54]. This question will examine how often the participants perform following activities: giving care or support, voluntary work, activities at home, sport activities outside a club, cultural activities, activities in an organization, going to a bar/restaurant/shopping center/trips, attend training. Also, low-key social participation will be examined by using 2 items from the questionnaire of Oswald and Konopik [58]. *Future perspective* will be assessed by using a self-constructed question and will explore to what extent the participant has things to look forward to. Finally, the occurrence of *life-events* will be assessed by using a shortened version (11 items) of the Geriatric Adverse Life Events Scale (GALES) [59, 60].

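### Preventing discontinuation of care is an effect objective, but the measures that record discontinuation are taken only in the experimental arm; both arms offer only a crude T0/T1 proxy

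*Protocol article*

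**What the plan says.** The objectives at the end of the Background fall into an effect evaluation and a process evaluation. The third effect question is whether the programme "prevents that care and support is discontinued", whether the older person or the organisation ends it, and so lowers dropout. Under Study design, "The RCT will compare usual care with an intervention that include tailored care and support and long-term care follow-up".

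The recording of discontinuation is described elsewhere:

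- Study design, text under Fig. 1: "The process evaluation will be performed by a quantitative monitoring of the experimental group", with follow-up telephone interviews included.
- Intervention: a municipal professional "will monitor which care the participant receives, when the older person cancels the care and support", monthly by telephone.
- Table 2: "Number refuses, dropouts and completions" and the logbook are process measures in the quantitative monitoring column, and reasons for refusal or dropout are in the monthly follow-up column. Of the study groups, only the experimental group is marked in those two columns. The control group is marked for T0, T1 and the qualitative evaluation.
- Process evaluation (Measurements): the dropout counted is dropout during the intervention.

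Both arms answer the T0 and T1 questionnaires. Under Secondary outcome measures, participants are asked "if they receive care from 7 informal (e.g., children, neighbors, friends) and 13 formal caregivers" and whether they are satisfied with that help. They are also asked whether help with eight daily activities is needed and sufficient. The effect-evaluation analysis regresses T1 scores on randomised group for every measure.

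**The concern.** To prevent or reduce something is a causal claim and needs a comparator. The protocol has a randomised comparator, but the instruments that see care being cancelled or refused are part of delivering or monitoring the intervention and do not reach the control arm.

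A low count in the experimental arm has at least three explanations: the programme worked, the background rate is low, or the people randomised were willing to start with. The last is plausible because the eligibility criteria require acceptance of the intervention before entry to the RCT. One arm's count cannot separate these. At stake is one of the four stated effect objectives. The primary outcomes are not affected.

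**Working it through.** **1. The plan's own figures.** The protocol gives no figure for discontinuation. Its sample-size statements reproduce: the exact two-sided t-test at 5% and 80% power needs 63.77 per group for d = 0.5 (stated 64) and 393.41 for d = 0.2 (stated 394). They do not bear on this point, which rests on comparing sections.

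**2. Objective against measurement.**

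| Element | Experimental | Control |
|---|---|---|
| Care cancelled, monthly calls | yes | no |
| Refusals, dropouts, completions, logbook | yes | no |
| Reasons for refusal or dropout | yes | no |
| Care sources (7 informal + 13 formal = 20), T0 and T1 | yes | yes |
| Need for and sufficiency of help, 8 activities, T0 and T1 | yes | yes |

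The first three rows record discontinuation, and the control column is empty. Dropout from the intervention cannot occur in the control arm at all. The last two rows are secondary outcomes, but neither is defined as discontinuation or tied to this objective.

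**3. What the monitoring measures alone can show.** With the experimental rate p_E known and the control rate p_C unobserved in [0, 1], the difference p_E - p_C lies in [p_E - 1, p_E]. The values of p_E are assumed.

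| p_E | Bounds on the difference |
|---|---|
| 10% | -90 to +10 points |
| 20% | -80 to +20 points |
| 30% | -70 to +30 points |

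**4. What the T0/T1 care items can show.** A source present at T0 and absent at T1 can be compared between arms. The approximate 95% half-width for a difference in proportions, with the same p in each arm, is 1.96 × sqrt(2p(1-p)/n).

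The protocol gives no expected size for the randomised arms: its 900 participants span four groups. For illustration, n = 198 is the 220 per group of the study cited in the power section, less its 10% loss (220 × 0.9). Only people with care at T0 can lose it, so n = 99 supposes that half of them have some.

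| n per arm (assumed) | p = 20% (assumed) | p = 30% (assumed) |
|---|---|---|
| 198 | 1.96 × sqrt(0.32/198) = 7.9 points | 1.96 × sqrt(0.42/198) = 9.0 points |
| 99 | 1.96 × sqrt(0.32/99) = 11.1 points | 1.96 × sqrt(0.42/99) = 12.8 points |

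**5. What the proxy misses.** The first effect objective targets people who lack the care they need, so much of the relevant care will start after T0. Care that starts and stops between visits is invisible to the proxy, as are the date of stopping, who stopped it and why. The proxy also counts recovery, or formal care replacing informal care, as a loss.

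**The case against.** The strongest reply is that the protocol already keeps the two evaluations apart. The effect study uses the outcome measures, and monitoring of the experimental group serves the process evaluation. Recording intervention dropout in one arm is ordinary process evaluation. Care receipt and sufficiency of help are secondary outcomes in both arms with a planned between-arm regression. Choosing the derived variable that answers an objective is commonly left to a fuller protocol or analysis plan, which is not shown.

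Much of this stands, and it rules out three stronger readings that a reader might infer:

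- *That no between-arm estimate is possible.* The T0/T1 care items allow one, though a crude one.
- *That the objective of guiding people to care also lacks a randomised answer.* It is largely covered by the secondary outcomes on care receipt and sufficiency of help and by their planned regression.
- *That the investigators intend to answer the continuity objective with an uncontrolled dropout count.* No section says so.

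The reply does not remove the mismatch. A later analysis plan can derive a variable from the existing items, but it cannot supply control-arm information on care begun and ended between visits that was never scheduled for collection. The continuity question is placed under the effect evaluation, while the measures that address it directly sit under the process evaluation.

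**Conclusion.** The point holds for the continuity objective only. As scheduled, the effect on discontinuation cannot be estimated from the measures that record it, and what remains is a T0/T1 proxy that the protocol does not name for this purpose. The size of the gap is the step from bounds 100 points wide (monitoring data alone) to a half-width of roughly 8 to 13 points (proxy). The latter range rests on assumed arm sizes of 198 or 99 and assumed discontinuation of 20-30%, none of which the documents give for this trial. The change should be made because a stated effect objective is affected and the remedy is cheap.

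**What to change.** Name one between-arm continuity outcome for this objective:

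- **Preferred:** a short T1 item, worded identically in both arms, on care started and stopped since T0, by whom and why.
- **Otherwise:** any care source present at T0 and absent at T1, among those with care at T0, read alongside sufficiency of help at T1 so that recovery or substitution is not taken for harm.

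Compare the arms by logistic regression with the T0 value, municipality and sample (the two census selections) as covariates. Keep logbook and monthly-call counts as descriptive process data with no effect claim. If no both-arm measure is added, restate the objective as descriptive under the process evaluation.

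The cost of the preferred option is a slightly longer T1 questionnaire and some recall error. The alternative needs only derived variables from data already collected, but it misses care that starts and stops between visits.
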